### Statistical analysis

The data from all participating centers will be combined for statistical analysis of the primary and secondary endpoints as well as AEs. The analysis will be done at Beijing Jiaotong University. Continuous variables will be presented as the mean ± SD. The comparability of the characteristics between the two study groups will be assessed using a two-samples Student’s *t* test for continuous variables and the χ^2^ test or Wilcoxon test, when appropriate, for categorical variables. The Wilcoxon paired signed-rank test will be used for within-group comparisons.

All randomized patients constituted the intention-to-treat population. All participants will be analyzed according to their original treatment allocation. Primary and secondary endpoint data will be collected for the entire follow-up period for all patients. Patients lost to follow-up will be considered at risk until the date of last contact, at which point they will be censored. Kaplan-Meier curves will be used to examine MACE-free survival time. The Cox proportional hazards model with covariates of treatment will be used for primary and secondary analyses. Hazard ratios and 95 % confidence intervals for each of the categories determined by age, sex, diabetes, and conventional therapy will be provided for the primary and secondary endpoints.

For all analyses, a value of *P* < 0.05 will be considered statistically significant, and all tests will be two-tailed. All analyses will be conducted using SAS software version 9.2 (SAS Institute, Cary, NC, USA).

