## Methods/design

### Study design

This study is registered in the Chinese Clinical Trials Registry (ChiCTR-IPR-14005475). It is a multicenter, double-blind, randomized, placebo-controlled clinical trial. This study complies with the principles of the Declaration of Helsinki and Good Clinical Practice guidelines. Written informed consent will be obtained from all patients prior to their participation in this study, and the recruited patients will be randomized to either the Xiyue capsule group or the placebo group. We will rigorously follow the Consolidated Standards of Reporting Trials (CONSORT) recommendations in reporting the results [17].

The trial will be conducted in 25 centers in China (see in ​Additional file 1). A total of 1100 participants will be recruited. After acquiring consent from the participants or their parents and/or legal guardians, the participants will be enrolled in the trial, which consists of a 1-week run-in period, a 24-week treatment period, and a 24-week follow-up period. An outline of the study procedures is illustrated in Fig. 1.

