### Randomization and blinding

Participants are randomized in a 1:1 ratio using a computer-generated, site-stratified, block randomization schedule. The study capsule will be labeled with sequential randomization numbers, and each patient will be assigned the lowest number available at each participating center. All patients, care providers, and attending physicians will be blinded to treatment assignment until the study is completed. The duplicated blinding codes will be given to the main research institution and the manufacturer to keep, and the blinding codes cannot be broken during the trial.

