### Sample size calculation

The sample size was calculated on the basis of expected reduction in cardiovascular events (cardiac death, all-cause mortality, reoccurrence of MI, and any form of revascularization). A previous study suggested that the incidence for all major clinical cardiovascular events combined at 1 year after interventional treatment of CHD is 12.8 % [20]. Therefore, the hypothesis of this study is to reduce the incidence of cardiovascular events to 7 % in the treatment group. Given a type I error rate of α = 0.05, a power of 80 % (type II error rate of β = 0.2), the sample size for one arm needs to be 447, resulting in *n* = 2 × 447 = 894 patients. Considering a dropout rate of 20 %, a total of 1097 patients needs to be allocated to reach the required number of patients for the efficacy analysis. For convenience of randomization, we decided to recruit 1100 patients. The formula used to calculate the sample size is as follows:$$ n=\frac{p_1\left(1-{p}_1\right)\kern0.5em +\kern0.5em {p}_2\left(1-{p}_2\right)}{{\left({p}_1-{p}_2\right)}^2}{\left(u{}_{\upalpha}+\kern0.5em u{}_{\upbeta}\right)}^2 $$$$ \mathrm{n}\approx 447\ \mathrm{patients}/\ \mathrm{group} $$

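### The Cox model names treatment as its only term, although randomization is stratified by site and plausible prognostic factors are collected: a modest loss of efficiency, not of validity

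*Protocol article*

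**What the plan says.** The Randomization and blinding section fixes the design: "Participants are randomized in a 1:1 ratio using a computer-generated, site-stratified, block randomization schedule". The Study design section gives the number of strata: "The trial will be conducted in 25 centers in China".

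The Statistical analysis section then sets the model for the time-to-event endpoints: "The Cox proportional hazards model with covariates of treatment will be used for primary and secondary analyses". It names no stratum for site and no baseline variable. Baseline characteristics appear only in the sentence that follows: "Hazard ratios and 95 % confidence intervals for each of the categories determined by age, sex, diabetes, and conventional therapy will be provided". That sentence describes hazard ratios by category, not adjustment of the main comparison.

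Table 1 shows demographic data, medical history and concomitant medications collected at screening. The inclusion criteria require enrollment within a year of PCI, so each site must know the PCI date to apply that criterion, although Table 1 does not list the interval as a data item.

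**The concern.** Two features of the design are not carried into the analysis.

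- **Site.** Blocking within site balances the arms within each center. An analysis that reflects this compares like with like inside the strata.
- **Baseline risk.** Patients aged 18 to 75, with or without diabetes and up to a year after PCI, plausibly differ in their risk of a major adverse cardiovascular event. Leaving a prognostic variable out of a Cox model moves the treatment hazard ratio toward 1 and does not raise power.

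At stake is how much information a trial with roughly 90 to 110 expected events draws from them. Timing also matters: covariates chosen after unblinding carry little weight. When the article was written, enrollment was open with 452 participants and no analysis had been done, so prespecification was still possible.

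**Working it through.** **Inputs from the article.** Control risk 12.8% and treated risk 7% at 1 year; 80% power; 447 per arm (894), inflated to 1097 and rounded to 1100 (Sample size calculation). "Given a type I error rate of α = 0.05", and "all tests will be two-tailed". Twenty-five sites, so 1100/25 = 44 patients per site.

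**The plan's own figure.** The printed formula gives (0.128×0.872 + 0.07×0.93)/0.058² × (1.96 + 0.8416)² = 412.3, so 413 per arm. The pooled-variance formula gives 416, and 449 with a continuity correction. The last is the closest to 447. Every variant compares two proportions, so the planned size assumes no gain from adjustment.

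**Implied hazard ratio and events.** HR = ln(0.93)/ln(0.872) = 0.530. Events needed for 80% power: 78 (Schoenfeld) or 84 (Freedman). Events expected: 447 × (0.128 + 0.07) = 88.5 at 894 patients, and 550 × 0.198 = 108.9 at 1100. Per site that is 88.5/25 = 3.5 to 108.9/25 = 4.4, or about 4.

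**Assumption.** The article does not say how prognostic the factors or the sites are. Prognostic strength is therefore assumed, as the standard deviation (SD) of the log-hazard due to covariates and to site, and varied over a range.

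**Simulation A.** Twenty-five sites, blocks of 4 (assumed), control risk held at 12.8%, conditional HR 0.530, no dropout. There were 2000 trials per row at N = 880 and 4000 otherwise. Cells show hazard ratio and power.

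| SD covariate / site | N | Treatment only | Site strata only | Covariate only | Both |
|---|---|---|---|---|---|
| 0 / 0 | 880 | 0.533, 81.2% | 0.533, 80.9% | 0.533, 81.1% | 0.533, 81.0% |
| 0 / 0.3 | 894 | 0.531, 81.4% | 0.530, 81.5% | 0.531, 81.4% | 0.529, 81.3% |
| 0 / 0.5 | 894 | 0.531, 82.4% | 0.526, 83.1% | 0.531, 82.3% | 0.526, 82.9% |
| 0.5 / 0.3 | 894 | 0.534, 81.6% | 0.532, 81.8% | 0.529, 82.7% | 0.527, 82.7% |
| 0.8 / 0.3 | 880 | 0.545, 78.7% | 0.544, 79.0% | 0.532, 81.5% | 0.529, 80.6% |
| 1.0 / 0.5 | 894 | 0.557, 77.1% | 0.553, 77.6% | 0.535, 82.0% | 0.526, 82.2% |
| 0.5 / 0.3 | 1100 | 0.533, 89.9% | 0.531, 90.0% | 0.528, 90.3% | 0.526, 90.2% |
| 1.0 / 0.5 | 1100 | 0.559, 85.4% | 0.556, 85.8% | 0.537, 89.3% | 0.528, 89.1% |

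**Simulation B.** 1100 patients, 20% loss, 800 trials per setting. With SD 0.8 for both site and covariates, treatment only gives 0.556 and 75.4%, site strata 0.547 and 76.8%, and both 0.529 and 81.8%. With site SD 0.5 and covariate SD 0.6, power is 83% unadjusted and 85% with both. With no heterogeneity, all models give 88%. The Monte Carlo standard error at 75% is √(0.75×0.25/800) = 1.5 points.

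**Where the gain comes from.** In the 1.0 / 0.5 row at 894, the covariate alone takes power from 77.1% to 82.0%, while site strata alone take it to 77.6%.

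**Validity.** With a true HR of 1 (N = 880, 2000 trials), the treatment-only model rejected in 4.6% (SD 0.5 / 0.3) and 4.8% (SD 1.0 / 0.5) of trials. The Monte Carlo standard error is √(0.05×0.95/2000) = 0.5 points, so neither figure can be told apart from 5%.

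**What the unadjusted hazard ratio estimates.** In the 1.0 / 0.5 scenario the population risk on treatment is 7.39%, so the marginal ratio is about ln(0.9261)/ln(0.872) = 0.561. The simulated 0.557 and 0.559 agree with it.

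**The case against.** **It belongs in the analysis plan.** Covariate lists and pooling rules are commonly left to a statistical analysis plan, and the plural in the model sentence is loose. This stands in part: a plan not shown may say more. But the article does specify the model's content, and treatment is the only term it gives, so this is a stated choice and not only an absent detail.

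**Pooling the centers does not show that site is ignored.** The article says: "The data from all participating centers will be combined for statistical analysis". This objection stands fully. A site-stratified Cox model also combines all centers. The point rests on the model sentence alone.

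**A reader might infer that the hazard ratio is biased or the test invalid.** The material does not support that. The hazard ratio is non-collapsible: the treatment-only model estimates a marginal effect and the adjusted model a conditional one. The null simulations show error at about the nominal level.

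**A reader might infer that the trial is underpowered.** That is not supported either. Treatment-only power falls below 80% only with strong assumed heterogeneity and the conditional HR fixed at 0.530, which makes the marginal effect smaller than the planned 12.8% versus 7%. The article nowhere calls the factors strong. Its eligibility limits on angina class, heart failure class, blood pressure, glucose, and renal and liver function narrow the spread of risk.

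**Conclusion.** The point holds as a mismatch between design and analysis with a modest efficiency cost. The mismatch itself can be read directly from the article. The cost rests on assumed SDs: nothing without heterogeneity, about 1 to 2 points of power under moderate heterogeneity, and about 4 to 7 points under very strong heterogeneity. At 894 patients the treatment-only hazard ratio exceeds the fully adjusted one by about 1% in the moderate case (0.534 against 0.527) and about 6% in the strongest (0.557 against 0.526). Site accounts for little of this, because about 4 events per site leave little to gain; the case for stratifying by site is mainly consistency with the randomization. This is a worthwhile recommendation, not an error that threatens the trial's conclusion.

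**What to change.** Before unblinding, replace the model sentence with a prespecified model for the primary and secondary endpoints:

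- a Cox model stratified by site, with a fixed rule, set on blinded data, for pooling sites with few patients or events;
- adjustment for baseline age and diabetes, plus time from PCI to randomization if the PCI date used for eligibility is recorded;
- the matching site-stratified log-rank test alongside the Kaplan-Meier curves;
- the treatment-only Cox model as a sensitivity analysis.

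The cost is a few sentences and one blinded decision on pooling. It needs no added patients, and no new data beyond confirming that the PCI date is held. There are two small downsides. The main hazard ratio becomes conditional and should be labelled so. Sparse sites contribute little within their strata, which is why the pooling rule is needed.

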## Discussion

In this trial, we will investigate whether the Xinyue capsule combined with conventional treatment reduces the incidence of MACE and improve quality of life among patients within 1 year after PCI. With the pleiotropic effects that encompass antioxidant, antiapoptosis, and improvement of insulin resistance, PQS was demonstrated to modify regional endothelial function, decrease oxidative stress and blood glucose, and induce angiogenesis [21–24]. In our previous studies, we have found that Xinyue capsules plus Chuanxiong capsules combined with conventional treatment can further reduce the incidence of cardiovascular events without any adverse effect in patients with ACS after PCI [16]. A small-sample clinical trial in which researchers recruited 100 patients with ACS after successful PCI showed that Xinyue capsules together with Western medicine treatment can improve cardiac function and quality of life [25]. These findings and observations serve as an impetus for large controlled trials to examine the effect of Xinyue capsules in patients with ACS after successful PCI. The present study is designed as a multicenter, double-blind, randomized, placebo-controlled, parallel-group superiority trial that will provide higher-powered evidence regarding long-term survival with the use of Xinyue capsules in addition to conventional treatment for patients with CHD after successful PCI.

Our study has some limitations. First, the study is being undertaken in China, so it is uncertain whether the relative effects of the trial drugs would be similar in other ethnic groups. The relatively short follow-up period is another limitation of the study.

To conclude, the aim of this trial is to demonstrate that Xinyue capsules plus conventional treatment will lead to a reduction in the incidence of MACE in patients with CHD after successful PCI and subsequently yield long-term benefit.

### Trial status

The trial was initiated in December 2014 and is currently open for enrollment. A total of 452 participants have been enrolled. However, no analysis has been conducted since the commencement of the trial.

## Abbreviations

ACS, acute coronary syndrome; AE, adverse event; CHD, coronary heart disease; CK, creatine kinase; CRF, case report form; ECG, electrocardiogram; hs-CRP, high-sensitivity C-reactive protein; MACE, major adverse cardiovascular event; MI, myocardial infarction; PCI, percutaneous coronary intervention; PQS, *Panax quinquefolius* saponin; QLQ, Quality of Life Questionnaire; SF-36, 36-item Short Form Health Survey; TCM, traditional Chinese medicine; ULN, upper limit of normal
